### Sample size

The sample size for the study was determined based on the falls rates and effect sizes obtained from previous trials on people with PD and the elderly [6,31,32]. For each sample size calculation, power was set at 80%, alpha set at 5%, and the drop-out rate was set at 15%. For falls, a sample size of 110 was thought to be required to detect a 20% difference between the groups, assuming a falling rate of 60% in the control group. For walking speed, a sample size of 74 was required to detect a 10% difference between the groups, assuming a mean (± SD) walking speed in the control group of 58.4 (12.0) m/min. For the "timed up and go" test, a sample size of 83 was thought to be required to detect a 10% difference between the groups, assuming a mean (± SD) timed up and go in the control group of 13.78 (2.99) sec. Thus, to ensure adequate statistical power for each of these outcome measures, the sample size for the study would optimally be 110 per group (total n = 330). Approximately 60 percent of control group participants are expected to fall between Test 1 (baseline) and Test 4 (12 months after therapy) with falls reduced to around 40% in the two active therapy groups.

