***Protective stepping in standing***
Practise taking quick, large steps in different directions. Practise responding quickly to a verbal cue to step, or to a tug or push in a known or unknown direction. Encourage attentional strategies, such as focussing on visualising big and fast steps in the direction of loss of balance.

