**Figure 1 F1:**
[figure not shown]
**Falls interview questions**.

The three falls outcomes that are the primary outcomes are (i) the number of fallers in each group (ii) the number of multiple fallers in each group and (iii) the falls rate over 12 months in each group. Secondary outcome measures will include the number of injurious falls, defined as a fall requiring a visit to a health service provider. Additional secondary outcome measures include mobility, measured by quantifying walking speed using the 6m walking test and the Timed Up and Go Test [36]. Activity limitations will be quantified using the United Parkinson's Disease Rating Scale sections II and III [37]. Quality of life will be measured using the Parkinson's Disease Questionnaire-39 (PDQ39) [38] and EuroQol-5D [39]. Changes in health-related QoL will be measured using both a PD-specific measure (PDQ-39) and a generic utility instrument (Euroqol-5D) administered at baseline, immediately post-intervention, 3 months, and 12 months. Safety during the intervention phase will be assessed by time to first fall, and monitoring of adverse events related to therapy.

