### Statistical analysis

Statistical analysis will be undertaken using IBM SPSS version 19.0 (SPSS Corp, Chicago, Ill, USA) and STATA 8 (Stata Corp, College Station, Tex., USA) statistical software. All analyses will be conducted on an intention-to-treat principle using all randomised participants. Demographic characteristics and baseline data will be summarised by descriptive statistics. For the primary outcome measures, the number of fallers and multiple fallers in each group will be compared by calculating relative risks. The number of falls and falls rate per person per year in the three groups will then be compared using negative binomial regression models. This approach takes into account all falls and adjusts for varying duration of follow-up [40,41]. As a safety measure, time to first fall during the intervention period will be analysed using Kaplan-Meier survival analysis, and comparisons between groups will be made using the Mantel-Cox log rank test. The continuously-scored secondary outcome measures at baseline and the follow-up appointments will be compared using analysis of covariance with baseline scores and intervention group entered as independent variables [42,43]. For categorical secondary outcome measures, relative risks will be used to analyse differences between the groups.

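### The only between-group fall comparison named for the 8-week intervention phase is a first-fall log-rank test; adding rate and hazard ratios with intervals would be a cheap improvement

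*Protocol article*

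**What the plan says.** Under Outcome measures, the protocol article gives two components of intervention-phase safety: "Safety during the intervention phase will be assessed by time to first fall, and monitoring of adverse events related to therapy".

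Under Statistical analysis, the fall component is fixed: "As a safety measure, time to first fall during the intervention period will be analysed using Kaplan-Meier survival analysis". The named method for setting one group against another is a log-rank test. That section names no hazard ratio, confidence interval or threshold of concern for this comparison. It names no group comparison for the adverse events.

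The same section uses negative binomial regression for the number and rate of falls, with the reason: "This approach takes into account all falls and adjusts for varying duration of follow-up". The falls rate is defined over 12 months.

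Injurious falls (those needing a visit to a health service provider) are a secondary outcome, with no counting window stated. The falls calendar is described as kept for the 12 months after therapy, whereas the Sample size section counts fallers from baseline to 12 months after therapy.

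**The concern.** The 8 weeks are when the active programmes place most physical demand on participants. The movement strategy table, for example, has them respond to a verbal cue to step "or to a tug or push in a known or unknown direction". If a programme causes harm through falls, it may appear as more falls among people who would have fallen anyway. A first-fall endpoint cannot show that: one fall in week 1 and one fall followed by several more are the same observation. Repeat falls matter enough elsewhere in the plan for multiple fallers to be a primary outcome.

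A log-rank test also returns a p-value. With few first falls expected in 8 weeks, that p-value alone says little about how much extra risk the data can exclude.

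**Working it through.** **Inputs.** From Sample size: 60% control fallers from baseline to 12 months after therapy, 40% in the active groups, 80% power, alpha 5% (taken as two-sided), 15% drop-out, 110 per group. From the Abstract: an 8-week intervention phase. Assumptions added here: a constant hazard of first fall, and pairwise comparison of one active group with control. The 60% is spread over 60 weeks (8 weeks plus 12 months) or, as a variant, over 52.

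**The plan's own figure.** For 60% v 40%, n = (1.96 + 0.8416)² × (0.6×0.4 + 0.4×0.6) / 0.2² = 7.849 × 0.48 / 0.04 = 94.2 per group. Allowing for drop-out, 94.2/0.85 = 110.8, against the stated 110. It reproduces to rounding. No event count or power is stated for the safety test. The range 94 to 110 below covers 15% loss (0.85 × 110 = 93.5) to none; little of that loss need occur within 8 weeks.

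**Eight-week risk.**
- 60-week base: weekly hazard −ln(0.4)/60 = 0.01527. Control risk 1 − exp(−8 × 0.01527) = 11.5%. With the hazard doubled, 21.7%.
- 52-week base: hazard −ln(0.4)/52 = 0.01762. Risks 13.1% and 24.6%.

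**Power and precision.** Events D = n × (control risk + active risk). Power = Φ(ln HR × √(D/4) − 1.96). If the true and observed hazard ratio are 1, the upper 95% limit is exp(1.96 × √(4/D₀)), with D₀ = 2n × control risk.

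| Base (weeks) | n per group | D at HR 2 | Power at HR 2 | D₀ | Upper limit at HR 1 |
|---|---|---|---|---|---|
| 60 | 94 | 31.2 | 49% | 21.6 | 2.32 |
| 60 | 110 | 36.5 | 55% | 25.3 | 2.18 |
| 52 | 94 | 35.5 | 54% | 24.7 | 2.20 |
| 52 | 110 | 41.5 | 61% | 28.9 | 2.07 |

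For a hazard ratio of 1.5, power is 18-23%. For 80% power at a hazard ratio of 2, 4 × 7.849 / (ln 2)² = 65.4, so 66 events are needed (Schoenfeld); Freedman's formula gives 71. Log-rank simulation (4,000 trials per scenario) gave 48-59% power.

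**Sensitivity to the 8-week control risk**, keeping proportional hazards and a hazard ratio of 2: a risk of 8% gives 37-42% power, 20% gives 71-78%, and 25% gives 80-85%.

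**Separate model: fall-proneness differs between people.** Assume gamma-distributed proneness with variance 1 to 3, a range not taken from the article. Solving (1 + θm)^(−1/θ) = 0.4 for the mean number of falls m on the 60-week base, then scaling by 8/60, gives 0.20 to 0.65 falls per control in 8 weeks, with 8-week risks of 16.7% to 30.3%. Per 110 controls that is about 18 first falls of 22 falls (θ = 1) to 33 of 71 (θ = 3), so 17% to 53% of falls are dropped.

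**What counting all falls gains.** For a rate ratio of 2, SE = √((1/m₀ + 1/m₁ + 2θ)/n), where m₀ and m₁ are the mean falls in 8 weeks. Ranges cover both bases and n = 94 to 110; the log-rank column is from simulation.

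| Heterogeneity | First-fall log-rank | All falls, negative binomial |
|---|---|---|
| None | 48-59% | 48-61% |
| Gamma variance 1-3 | 36-60% | 59-75% |

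**The case against.** The best case for the plan has four parts.

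- **First falls are not the whole safety plan.** A reader might infer that intervention-phase safety ignores injuries. The article does not support that: adverse events related to therapy are monitored too, and an injurious fall judged related would be captured there. What stands is narrower: capture depends on a judgement of relatedness, and no between-group comparison is named.
- **Nothing says that p > 0.05 will be read as no harm.** That is correct. The point is only that the named output makes such a reading possible. Kaplan-Meier curves do estimate the fall-free proportion in each group, and a hazard ratio may be specified in a fuller document. The stated endpoint and test are still what the article fixes.
- **Injurious falls may cover the 8 weeks.** A reader might infer from the calendar that they are counted only after therapy. No window is stated, the faller count used for sample size starts at baseline, and the safety analysis needs fall dates within the phase. Exclusion is a possible inference, not a fact.
- **Time to first fall is a legitimate summary, and the alternative is also underpowered.** It is not dominated by a few very frequent fallers, and using another summary for safety is no contradiction. The trial was sized on falls, walking speed and timed up and go, not on harm. This objection stands, and it is why the remedy adds to the planned analysis and relies on intervals.

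The constant-hazard interval and the share of falls dropped under heterogeneity come from different models and should not be combined as one worst case.

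**Conclusion.** The point holds as a cheap improvement, not as an error that undermines the trial. For the 8-week phase, the one named between-group fall comparison discards repeat falls and comes without a named effect estimate. On the article's planning figures and a constant hazard, a true doubling of first-fall hazard would be missed in about 40-50% of trials, and equal observed risk would leave a doubling inside the 95% interval.

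The size rests on the derived 8-week control risk of 11.5-13.1%. If that risk were about 25% with proportional hazards, power would reach about 80%. If a higher early risk came instead from differing fall-proneness, proportionality would fail and simulated power stays at 36-60%. Counting all falls raises power mainly when falls cluster in some people, and in none of the scenarios computed does it reach 80%.

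**What to change.** - Keep Kaplan-Meier and the log-rank test, and add a hazard ratio with its 95% interval for each active arm v control.
- Compare all falls in the 8 weeks, each active arm v control, by the negative binomial model already planned, as rate ratios with 95% intervals.
- Tabulate repeat falls and falls needing a health-service visit by arm for the phase. The article gives no rate for the latter, so a table is safer than a model.
- Base the safety statement on the upper confidence limits, and state that a non-significant test is not evidence of safety.
- Reconcile Sample size, Outcome measures and Statistical analysis on whether, and how, all falls in the 8 weeks are recorded. The all-falls comparison depends on this.

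The cost is a little more analysis and some wording, if every fall in the phase is already being recorded. The drawback is that the intervals will be visibly wide.

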**Methods/Design:**

People with idiopathic Parkinson's disease who live at home will be recruited and randomly allocated to one of three groups. Each person shall receive therapy in an out-patient setting in groups of 3-4. Each group shall be scheduled to meet once per week for 2 hours for 8 consecutive weeks. All participants will also have a structured 2 hour home practice program for each week during the 8 week intervention phase. Assessments will occur before therapy, after the 8 week therapy program, and at 3 and 12 months after the intervention. A falls calendar will be kept by each participant for 12 months after outpatient therapy.

Consistent with the recommendations of the Prevention of Falls Network Europe group, three falls variables will be used as the primary outcome measures: the number of fallers, the number of multiple fallers and the falls rate. In addition to quantifying falls, we shall measure mobility, activity limitations and quality of life as secondary outcomes.

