### Participants

Community dwelling people with PD will be recruited for the trial from outpatient movement disorder clinics, community-based rehabilitation programs, PD support groups and private neurologists in the Melbourne metropolitan area. Participants will also be recruited from the local community through advertisements in local and metropolitan newspapers and newsletters distributed by Parkinson's Victoria, Australia. Potential participants will be provided with an information pack describing the study, and invited to return an 'expression of interest' to the study coordinator to be screened for eligibility. To be included, participants will be required to have confirmed idiopathic PD, be able to participate in an outpatient exercise program including strength training and be willing to complete a falls calendar for 12 months after therapy. Participants will be excluded if they score less than 24 on the Mini-Mental State Examination (MMSE) [29], or if they have a rating greater than 4 on the modified Hoehn and Yahr scale [30] or if they are on major tranquilizers.

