### Outcome measures

All participants will be tested by trained blinded assessors before and after the 8 week interventions, and at 3 months and 12 months after completion of the intervention phase. Participants will keep a falls calendar for 12 months after therapy. Consistent with the recommendations of the Prevention of Falls Network Europe (PrOFaNE) group, a fall will be defined as "an unexpected event in which the participant comes to rest on the ground, floor, or lower level" [35]. Each time a participant falls, they will tick the date on the falls calendar and then telephone a falls hotline where they will be interviewed about the nature of the fall, circumstances, injuries sustained, healthcare required and other factors. The falls interview questions are given in Figure 1, and an example of a calendar page is provided as an additional file (see Additional File 1).

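### The safety endpoint, time to first fall during the 8-week intervention, lies wholly outside the stated window of the only dated falls record the article describes

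*Protocol article*

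**What the plan says.** **The endpoint.** The Outcome measures section says: "Safety during the intervention phase will be assessed by time to first fall, and monitoring of adverse events related to therapy". The Statistical analysis section repeats it: "As a safety measure, time to first fall during the intervention period will be analysed using Kaplan-Meier survival analysis", with groups compared by the log-rank test. The abstract gives the length of the intervention: "Each group shall be scheduled to meet once per week for 2 hours for 8 consecutive weeks".

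**The falls record.** Three places give the window of the calendar, and all three put it after therapy:

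- Abstract, Methods/Design: "A falls calendar will be kept by each participant for 12 months after outpatient therapy".
- Participants, as a condition of entry: "be willing to complete a falls calendar for 12 months after therapy".
- Outcome measures: "Participants will keep a falls calendar for 12 months after therapy".

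Outcome measures also explains how a fall acquires a date: "Each time a participant falls, they will tick the date on the falls calendar and then telephone a falls hotline". No other dated falls record is described.

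**The planning assumption.** The Sample size section uses a different window. Its 60% of control participants falling refers to the time from Test 1 (baseline) to Test 4 (12 months after therapy), so the intervention weeks are included.

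**The concern.** Kaplan-Meier curves and a log-rank test need, for each participant, either the date of the first event or the length of time known to be event-free. Both must come from a record kept while the time at risk is running. Here that time is the 8 weeks of therapy, and the calendar as described opens only when those weeks are over.

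Followed literally, the data collection cannot supply the safety analysis. Falls that nobody recorded prospectively cannot be recovered later by an analysis plan. The question at stake is whether the groups differ in how soon people fall while the programmes are being delivered.

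A second matter follows from the same ambiguity. If falls are recorded from baseline, as the sample size assumption implies, a reader cannot tell whether those in the first 8 weeks enter the primary falls outcomes. The primary falls rate is described as covering 12 months.

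**Working it through.** **1. Compare the windows.** Count weeks from baseline, taking 12 months as 52 weeks and ignoring any gap between baseline testing and the first class.

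| Item | Section | Weeks covered |
|---|---|---|
| Safety endpoint | Outcome measures; Statistical analysis | 1 to 8 |
| Calendar and hotline | Abstract; Participants; Outcome measures | 9 to 60 |
| Falls assumed for sample size | Sample size | 1 to 60 |

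The first two rows do not overlap. The third covers both, so it agrees with neither. The intervention is 8/60 = 13% of the sample size window.

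**2. Look for another source in the text.** Monitoring of adverse events is the only candidate. It is listed beside time to first fall as a separate item, and it is limited to events related to therapy. A fall at home in the life-skills group need not qualify, and no method of dating falls from this monitoring is given. The assessments before and after the 8 weeks are not described as collecting falls.

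**3. Reproduce the plan's own falls figure.** Inputs from the Sample size section are 60% v 40%, 80% power, 5% alpha (taken as two-sided) and 15% drop-out. With unpooled variance:

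n = (1.960 + 0.842)² × (0.6×0.4 + 0.4×0.6) / 0.20² = 94.19 per group

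94.19 / 0.85 = 110.8

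This agrees with the stated 110 to within one participant. The figure is not in dispute, and the 60% and 40% can be carried forward as the plan's own assumptions.

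**4. Illustrate how many first falls lie in the 8 weeks.** Assume a constant hazard from baseline to Test 4. The article does not state this; it is an assumption made here.

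- Controls, window of 60 weeks: hazard = −ln(0.4)/60 = 0.01527 per week. Risk in 8 weeks = 1 − exp(−8 × 0.01527) = 11.5%, and 0.115 × 110 = 12.7.
- Controls, taking the intervention as 2 months of 14: hazard = −ln(0.4)/14 = 0.0654 per month. Risk = 1 − exp(−2 × 0.0654) = 12.3%, and 0.123 × 110 = 13.5.
- Active groups at 40%, window of 60 weeks: hazard = −ln(0.6)/60 = 0.00851 per week. Risk = 1 − exp(−8 × 0.00851) = 6.6%, and 0.066 × 110 = 7.2.

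So about 13 first falls in the control group and about 7 in each active group would be the events for this analysis. The calendar in its stated window would record none of them. The active-group figure also assumes that the planned benefit applies from the first week, so it is the weaker of the two.

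**The case against.** This is a condensed article, and the form used to record falls during therapy is operational detail that a full protocol may hold. Saying that a calendar is kept for 12 months after therapy does not say that earlier falls go unrecorded. The sentence on ticking the date and telephoning carries no time limit. The Sample size section counts falls from baseline, which suggests that recording from baseline was intended. Participants in all three arms attend weekly, so a dated record would be easy to keep.

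Much of this stands. A reader might infer that the endpoint has no data source at all, and the article does not support that: it shows only that none is described. A reader might also infer that intervention-phase falls would be known only from unblinded therapists, so that the log-rank test would measure reporting and not risk. Nothing in the text says so. Nor is there support for supposing that a given share of falls would be missed in one arm only. Any bias between arms depends on how falls were otherwise reported, and the article is silent on that.

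What does not stand is the view that this is merely omitted detail. The calendar window is not left out. It is stated three times, once as an entry condition, and each time it excludes the period of the endpoint. If recording from baseline was intended, those three statements are wrong and still need correction.

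**Conclusion.** The point holds as a contradiction between stated windows. Time to first fall during the intervention is to be analysed by Kaplan-Meier and log-rank methods, but the only dated falls record described begins after the intervention ends, and the Sample size section implies yet another window. Adverse event monitoring as described does not fill the gap in all three arms.

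On the plan's 60% and an assumed constant hazard, about 11.5% to 12.3% of controls, or about 13 of 110, would have the event in a period that the calendar does not cover. This shows the scale of what is at issue; it does not estimate a bias.

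Severity is should-fix. A reader might take the mismatch as a threat to the primary falls analysis, but the calendar and hotline cover the 12 months after therapy on which the falls rate is based. What is needed for the primary outcomes is a clear statement of their window.

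**What to change.** - Start the same calendar and hotline at Test 1 in all three arms, and say that the safety analysis uses them.
- Give one time origin for time to first fall, the same in every arm and covered by the calendar, with censoring at Test 2 or withdrawal.
- State whether the three primary falls outcomes count only the 12 months after therapy or also falls during the intervention. Without this, an earlier calendar start could blur the 12-month falls rate.
- Bring the calendar wording in the abstract, Participants and Outcome measures into line with the baseline-to-Test 4 window in Sample size and with the safety endpoint in Outcome measures and Statistical analysis.

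The cost is about two more months of calendar keeping per participant, some extra hotline calls, and a change to the entry condition on calendar completion. The timing matters more than the cost, because falls before the calendar starts cannot be dated reliably afterwards.

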## Discussion

This RCT will be one of the first investigations of the effects of physical therapy interventions on falls in people with idiopathic PD. It will also be one of the first PD studies to collect detailed data on falls over a 12 month period, using a falls calendar coupled with telephone interviews. This will provide an accurate record of falls rates in a large cohort from a major metropolitan city. It will also provide data on the contributing factors to falls in people with PD and the injuries sustained and healthcare required. Such data are not currently available and will be of benefit to policy makers, healthcare professionals and people living with PD. Data are also being collected on impairments, disability and quality of life, allowing examination of the associations between these variables and falls frequency and severity in PD.

There are a number of limitations of the current trial. Participants will all be rated 0-IV on the modified Hoehn and Yahr Scale [30] and therefore the results cannot be generalised to those rated V, who are severely disabled. All measurements will be taken during the day at peak dose of the levodopa medication cycle and therefore the effects of medication cannot be separated from the effects of physical therapy and falls education. The response to strength training, strategy training or life-skills social interventions in the "off' phase of the levodopa cycle cannot be ascertained. Moreover the results can only be generalised to outpatient therapy services and may not be directly applicable to home or hospital care.

